## Abstract

**Background:**

Pylorus-preserving pancreaticoduodenectomy (ppPD) is a standard surgical procedure for the treatment of resectable neoplasms of the periampullary region. One of the most common postoperative complications after ppPD is delayed gastric emptying (DGE) which reduces quality of life, prevents a timely return to a solid oral diet and prolongs the length of hospital stay. In a retrospective analysis, intraoperative endoluminal pyloromyotomy was associated with a reduced rate of DGE. The aim of this study is to investigate the effect of intraoperative endoluminal pyloromyotomy on postoperative DGE after ppPD in a randomised and controlled setting.

**Methods:**

This randomised trial features parallel group design with a 1:1 allocation ratio and a superiority hypothesis. Patients with a minimum age of 18 years and an indication for ppPD are eligible to participate in this study and will be randomised intraoperatively to receive either endoluminal pyloromyotomy or atraumatic stretching of the pylorus. The sample size calculation (*n*=64 per study arm) is based on retrospective data. The primary endpoint is the rate of DGE within 30 days. Secondary endpoints are quality of life, operation time, estimated blood loss, length of hospital stay, morbidity and mortality.

**Discussion:**

DGE after ppPD is a common complication with an incomplete understood aetiology. Prevention of DGE could improve outcomes and enhance quality of life after one of the most common procedures in pancreatic surgery. This trial will expand the existing evidence on intraoperative pyloromyotomy, and the results will provide additional data on a simple surgical technique that could reduce the incidence of postoperative DGE.

**Trial registration:**

German Clinical Trials RegisterDRKS00013503. Registered on 27 December 2017.

## Background

Partial pancreaticoduodenectomy (PD) is considered standard therapy for resectable malignant neoplasms of the pancreatic head, distal common bile duct and papilla of Vater as well as precursors with malignant potential, such as intraductal papillary mucinous neoplasia (IPMN). The classical partial pancreaticoduodenectomy with resection of the distal stomach was modified by Traverso in the 1970s by introducing the pylorus-preserving technique (pylorus-preserving partial pancreaticoduodenectomy ppPD) [1]. Both procedures have been shown to be equally effective in terms of morbidity, overall survival and tumour recurrence [2, 3].

One of the most common complications after both procedures is a delayed gastric emptying (DGE) affecting up to 61% of patients [4]. Although DGE is not a lethal complication, it is associated with reduced quality of life and prolonged length of hospital stay [5, 6]. Severe cases may even lead to delayed initiation of subsequent therapeutic measures such as adjuvant chemotherapy [6].

DGE after PD was first described by Warshaw and Torchiana in 1985, but prior to the introduction of the International Study Group of Pancreatic Surgery (ISGPS) definition of DGE in 2007, the term was inconsistently defined by different authors, which severely limited the comparability of studies on DGE until then [7, 8].

The underlying mechanisms of DGE are not yet fully elucidated, but spasm of the pyloric muscle, devascularisation of the pylorus and postoperative hormonal changes may contribute to the development of DGE [9–12]. Intra-abdominal complications such as pancreatic fistula, anastomotic leakage and formation of haematoma or abscess have been associated with the development of DGE in several studies [13–15].

Various modifications including route of reconstruction, pyloric dilatation, pyloric resection and their impact on DGE have been studied with conflicting results [4, 16–19]. Meta-analyses and larger randomised trials using the “International Study Group of Pancreatic Surgery” definition of DGE failed to demonstrate an association between modifications studied and DGE [4, 20–22].

Pyloromyotomy during ppPD was first investigated by Kim et al. who performed a Fredet-Ramstedt type pyloromyotomy and antroplasty in 47 consecutive patients undergoing ppPD [9]. The reported DGE incidence of 2.2% can be partially explained by the underlying strict individual definition of DGE consisting of the inability to tolerate any oral intake, including a liquid diet, for three consecutive days in the absence of any attributable complications. However, a comparison with patients from the same institution treated by the same authors before the introduction of Fredet-Ramstedt pyloromyotomy showed a reduction in DGE rates with pyloromyotomy. Furthermore, endoscopic approaches to gastroparesis support the idea of performing endoluminal pyloromyotomy to reduce DGE [23–25]. In gastroparesis with underlying increased pyloric tone and pylorospasm, peroral endoscopic endoluminal pyloromyotomy can permanently improve gastric emptying [26]. Assuming that pylorospasm and pyloric dysregulation play a role in the development of DGE, we introduced an intraoperative endoluminal pyloromyotomy for patients undergoing ppPD at our institution several years ago. A retrospective analysis of our technique showed that intraoperative pyloromyotomy was associated with a significant reduction in DGE in a multivariate analysis [27]. These promising results encouraged us to further investigate our findings in prospective and randomised trial.

### Objectives

This is a randomised single-centre trial of patients undergoing pancreaticoduodenectomy with a superiority hypothesis: intraoperative pyloromyotomy is associated with less DGE compared to multidimensional atraumatic stretching of the pylorus. The results of this trial may provide additional evidence for the discussion on surgical approaches to reduce DGE and could have an impact on a commonly performed operation in pancreatic surgery.

## Methods

### Trial design

This randomised trial features parallel group design with a 1:1 allocation ratio and a superiority hypothesis (intraoperative endoluminal pyloromyotomy during ppPD is associated with a reduced DGE rate compared to multidimensional atraumatic stretching of the pylorus). The flowchart of the study is visualised in Fig. 1.

**Fig. 1 Fig1:**
[figure not shown]
Trial flow chart

### Study setting and population

The study is conducted as a single-centre trial at the University Hospital Augsburg, Germany.

### Eligibility criteria

Patients with a minimum age of 18 years and an indication for a ppPD irrespective of the underlying disease who are scheduled for an elective surgery are eligible to participate in this study. All patients must provide written informed consent prior to participation. Patients who are unable to give consent, patients under legal guardianship, and patients participating in another intervention study that has a potential impact on the endpoint of this study will be excluded from participation.

### Informed consent and recruitment

All patients must provide written informed consent prior to participation. Informed consent for study participation and data collection will be obtained preoperatively by a surgeon at the University Hospital Augsburg. To ensure sufficient participant enrolment to achieve the sample size patients, scheduled for ppPD will be offered participation in the trial at the time they provide informed consent for surgery. Informed consent for study participation will be obtained during the explanation of the planned surgical procedure and the study intervention. Written information about the surgical procedure itself and the study intervention will be provided to support informed consent.

### Endpoints

#### Primary endpoint

The primary endpoint is defined as the rate of DGE according to the ISGPS definition within 30 days after ppPD. The two study groups (pyloromyotomy vs. no pyloromyotomy) are compared with respect to the primary endpoint.

#### Secondary endpoint

Secondary endpoints include the grade of DGE according to the ISGPS definition (proportion of with DGE Grade A, B, or C, see definition below), operative time (minutes), estimated blood loss (millilitres), overall morbidity (absolute number of complications and percentages in each group) according to the Clavien-Dindo classification [28] in-hospital mortality (absolute number of deaths and percentages in each group, cause of death), length of hospital stay (days from day of surgery to discharge), rate of primary DGE (defined as DGE in the absence of intraabdominal complications, absolute numbers, percentages) and postoperative quality of life. Serious adverse events will be documented, absolute and relative frequency, severity and relationship to the intervention will be reported and compared between intervention groups. Quality of life assessment in this study will be performed with the *European Organisation for Research and Treatment of Cancer* (EORTC) *Quality of Life Questionnaire Core 30* (QLQ-C30), a valid and widely used questionnaire in cancer patients [29], in combination with the supplementary module for patients with pancreatic cancer QLQ-PAN26. Quality of life data are assessed preoperatively and postoperatively on days 7, 14, 30, and 90. The assessment schedule is visualised in the SPIRIT figure (Table 1).

**Table 1 Tab1:** Schedule of enrolment, intervention and assessment

Timepoint/period	Study period						
	Day before surgery	During surgery	During hospital stay	POD 7	POD 14	POD 30	POD 90
Eligibility screening	**X**						
Informed consent	**X**						
Randomisation and allocation		**X**					
Intervention (both arms)		**X**					
Assessment of quality of life	**X**			**X**	**X**	**X**	**X**
Assessment of primary and secondary endpoints		**X**	**X**				

*POD* postoperative day

### Definition of delayed gastric emptying

For this study, the ISGPS definition of DGE was applied [8]. Grade A DGE was present if the nasogastric tube (NGT) was still in place or reinserted between postoperative days (POD) 4 and 7, or if the patient was unable to tolerate a solid oral diet by POD 7. Patients were found to have grade B DGE if the NGT was still in place or reinserted between POD 8 and POD 14, or if the patient could not tolerate a solid oral diet by POD 14. If the NGT was still in place or reinserted after POD 14, or if the patient could not tolerate a solid diet by POD 21, the DGE was classified as grade C in accordance with the ISGPS definition.

### Surgical procedures

Participating patients will be randomised intraoperatively after confirmation of absence of macroscopically visible metastases and technical resectability with pylorus preservation. The duodenum is transected 2 to 4 cm distal to the pylorus with a linear stapling device. Pancreaticojejunostomy and hepatojejunostomy are performed with end-to-side anastomoses. One of two different surgical manoeuvres is performed prior to the creation of the duodenojejunostomy, depending on the results of randomisation. In patients randomised to the “pyloromyotomy group”, an endoluminal pyloromyotomy using electrocautery is performed to transect the mucosa, submucosa and circular pyloric muscle anteriorly and posteriorly at the 12 and 6 o’clock positions (Fig. 2). In patients randomised to the “no pyloromyotomy group”, a Gross-Maier dressing forceps is used to atraumatically stretch the pyloric muscle before creating the duodenojejunostomy. The duodenostomy is performed by creating an end-to-side anastomosis with a single-layer running monofilament atraumatic suture technique. In all patients, reconstruction is performed with an omega loop in an antecolic fashion and a side-to-side Braun jejunostomy approximately 15 cm distal to the duodenojejunostomy. A nasogastric tube is placed in the stomach during the operation. The nasogastric tube is removed on the first postoperative day unless medical reasons prevent the removal of the nasogastric tube. The procedures were performed by or under the direct supervision of board-certified pancreatic surgeons who meet criteria for pancreatic competence centres set by the German Society for General and Visceral Surgery.

**Fig. 2 Fig2:**
[figure not shown]
Intraoperative endoluminal pyloromyotomy

### Methods against bias

#### Randomisation

Randomisation will minimise selection bias and potential confounding. Participants will be randomised intraoperatively after absence of macroscopically visible metastases and technical resectability with pylorus preservation has been confirmed. If premature randomisation has occurred and neither pyloromyotomy of stretching of the pylorus can be performed, randomisation will be discarded, the participant will be excluded from the study and no further data will be collected. If the intraoperative findings result in a total pancreatectomy, the patients will be excluded from the study and the randomisation, if already performed, will be discarded, the participant will be excluded from the study and no further data will be collected. Allocation to one of the two study arms will be carried out using a web-based randomisation tool which generates a random allocation sequence (https://www.randomizer.at). Block randomisation will be performed to ensure equal-sized groups. The size of the individual blocks will only be disclosed after the study has been completed so as not to allow prediction of group allocation. A sufficient number of subjects will be recruited according to the sample size calculation to prevent random errors and to ensure sufficient power to test the hypothesis of the primary endpoint. Randomisation will be performed by individuals not involved in the surgical procedure, data evaluation, data analysis, postoperative care, and follow-up of the patients.

#### Blinding

Patients as well as individuals involved in data collection, endpoint assessment and quality of life assessment will be blinded to group allocation to reduce information and measurement bias. As the study intervention is performed as part of a surgery under general anaesthesia and the study intervention is neither visible nor disclosed to the patient, patients can be considered blinded. Participating surgeons will be instructed which treatment procedures are applicable in each group. Blinding of surgeons is not feasible due to the nature of the interventions. Unblinding is possible in case of urgent medical reasons. If the treating surgeon and one of the investigators jointly decide that unblinding is necessary, unblinding can be done by any person authorised to randomise.

#### Intraoperative and postoperative management

Standardised instruction of participating surgeons in the application of the trial interventions reduce performance bias. All patients receive 100 μg of somatostatin subcutaneously intraoperatively at the time creation of the pancreaticojejunostomy and 100 μg of somatostatin subcutaneously three times daily thereafter until postoperative day 5, based on the internal standard.

### Sample size calculation

The sample size calculation is based on the primary endpoint "rate of delayed gastric emptying". A retrospective analysis from all patients who underwent ppPD at our institution between 2015 and 2017 revealed a DGE rate of 40.9% in patients who received intraoperative pyloromyotomy compared to a DGE rate of 66.7% in patients who did not receive pyloromyotomy, a difference in absolute risk of 25.8%. The calculation was carried out according to the method described by Campbell et al. for two-group assessments with binary outcomes [30]. Based on these figures, a sample size of 58 patients per treatment group is required to ensure a power of 80% at a two-sided significance level of 5%. To compensate for potential dropouts that would lead to dilution of the treatment effect, an additional 10% of patients will be recruited and randomised. Thus, 64 patients per group will be enrolled, resulting in a total number of 128 patients.

### Data collection

All data will be documented in hard copy case report forms. Quality of life data are recorded using the EORTC QLQ-C30 form in combination with the supplementary module for pancreatic cancer QLQ-PAN26. Both forms can be obtained from the *European Organisation for Research and Treatment of Cancer* (www.eortc.org). The completed CRFs will be reviewed by one of the investigators or an authorised sub-investigator. All data collected according to the study protocol will be manually transferred from the case report forms to an electronic SPSS file (IBM, Armonk NY, USA). Regular reviews of the correct data transfer are conducted by assessors at the study site. The electronic data will be stored in a protected folder on a server at University Hospital Augsburg. Paper-based data are stored in a locked office at the study site. In order to improve participant retention and collection of follow-up data, participants will be reminded regularly to complete the quality-of-life questionnaires.

### Pseudonymisation

Data is assessed and analysed in pseudonymised form. For this purpose, a randomly generated numerical four-digit code is assigned to each participant. Access to the original data and the pseudonymisation lists is restricted to the staff of the Department of General-, Visceral and Transplant Surgery at the University Hospital Augsburg. All identifying data will be deleted as soon as they are no longer used for research. The trial coordinators, the investigators and independent statisticians of the trial will have access to the final dataset.

### Data monitoring, data management and patient safety

The trial intervention is a low harm intervention that has been routinely performed at our institution for several years before initiation of the trial. A retrospective analysis of the study intervention which has been published did not reveal any safety concerns [27]. Therefore, there is no anticipated harm and no compensation for trial participation. Any complications will be reported to the Ethics Committee as part of the final report and included in the publication of the study results. Even without trial participation, patients who undergo pylorus-preserving pancreaticoduodenectomy at our institution will receive either pyloromyotomy or stretching of the pylorus as part of the routine surgery depending on the preference of the surgeon in charge.

To improve data quality, several measures were implemented. An internal data monitoring during the study is carried out by individuals not involved in data collection, patient recruitment or randomisation, but who have sufficient knowledge in conducting clinical trials. Annual reports on the participation rate and the status of the follow-up will be prepared. Data monitoring will be discussed with the investigators to review the progress of the study address potential problems. As part of the data monitoring process and to ensure proper data transfer from raw data and paper case report forms to data sets, all collected study data are entered into two electronic data sets by different persons. These two parallel data sets are compared at the end of the study using a computerised process. Any discrepancies between the two data sets are manually checked and corrected. An independent close-out audit is conducted before the data analysis, after the follow-up for the last participant has been completed.

### Data analysis plan

Continuous data will be presented as mean ± standard deviation or median with interquartile range, depending on the distribution. Categorical data will be presented as numbers with percentages. Approximately normally distributed continuous variables will be compared using the independent *t*-test. Non-normally distributed continuous variables will be compared using the Mann-Whitney-*U* test. Categorical data including the primary endpoint will be compared using the *χ*^2^ test. Fisher’s exact test will be used for categorical data if the requirements for *χ*^2^ test are not met. A two-sided *P* < 0.05 is considered significant. The primary analysis will be conducted in an intention-to-treat (“as randomised”) population. Discarded randomisations as defined in the randomisation section will be excluded from analysis. A multivariate analyisis of the primary endpoint will be performed which will include risk factors with a potential association with DGE (*P* < 0.15). Quality of life data will be analysed in accordance with the EORTC QLQ-C30 scoring manual [31]. An interim analysis was omitted because a sample size calculation was performed, and the study intervention regularly performed in ppPD at our institution is considered a low harm intervention that was not associated with an increased complication rate in a retrospective analysis. A subgroup analysis is performed for patients without intra-abdominal complications to assess the rate of DGE in this patient population.

Cases with missing data for the primary endpoint data resulting from the inability to assess the primary endpoint will be excluded from the primary endpoint analysis. Possible reasons for not being able to assess the primary endpoint are death of a participant before POD 7, unless the patient was able to tolerate a solid diet at that time (see ISGPS definition of DGE above), and the occurrence of a lymphatic fistula with the need for total parenteral nutrition.

Missing quality of life data will be addressed according to the recommendations of the EORTC scoring manual for quality-of-life questionnaires.

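### The supporting multivariate model selects risk factors by P<0.15 without limiting them to pre-randomisation factors, and the complication-free subgroup is not a randomised comparison

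*Protocol article*

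**What the plan says.** The Data analysis plan compares the primary endpoint between arms with an unadjusted χ² test (Fisher's exact test as fallback) in the as-randomised population. It then adds a multivariate analysis of the primary endpoint "which will include risk factors with a potential association with DGE", with P<0.15 as the stated criterion. It gives no candidate list and no restriction by time of measurement.

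The same section states: "A subgroup analysis is performed for patients without intra-abdominal complications to assess the rate of DGE in this patient population". The Secondary endpoint section lists a related outcome, primary DGE, meaning DGE without intra-abdominal complications, as absolute numbers and percentages.

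Two other sections bear on timing. The Background says: "Intra-abdominal complications such as pancreatic fistula, anastomotic leakage and formation of haematoma or abscess have been associated with the development of DGE". Under Surgical procedures: "Participating patients will be randomised intraoperatively after confirmation of absence of macroscopically visible metastases". The allocated manoeuvre is carried out before the duodenojejunostomy is made. Fistulas, leaks, haematomas and abscesses are therefore events after randomisation.

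**The concern.** In a randomised comparison there is no systematic confounding for a P-value screen to remove. Screening makes the covariate set, and hence the adjusted estimate, depend on the data. It also lets in unrelated factors by chance.

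The more serious matter is which factors the rule can admit. The DGE correlates that the article itself names are postoperative. If such a variable enters the model and the arms differ in it, the treatment coefficient no longer estimates the total effect of pyloromyotomy on DGE, which is what the trial is designed to measure. The complication-free subgroup has the same difficulty: membership is decided after randomisation, so its two arms are not the groups that randomisation formed.

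At stake is the reading of the supporting result. The Discussion cites univariate and multivariate analyses together as support for the retrospective finding, so the trial's own pair of results may well be read in the same way. A disagreement between them could then be an artefact of the model.

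**Working it through.** **Inputs from the article (Sample size calculation).** DGE 40.9% with and 66.7% without pyloromyotomy; two-sided 5%; power 80%; 58 per arm, raised by 10% to 64.

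**Reproducing the plan's figure.** The mean rate is (0.409 + 0.667)/2 = 0.538.

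n = [1.960·√(2·0.538·0.462) + 0.842·√(0.409·0.591 + 0.667·0.333)]² / 0.258² = (1.382 + 0.573)² / 0.0666 ≈ 57.4, so 58. Then 58 × 1.10 = 63.8, so 64. Both agree with the article. The planned log odds ratio is ln[(0.409/0.591)/(0.667/0.333)] = −1.06.

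**Assumptions, not in the article.** Complication rates by arm, and an odds ratio of 5 between complication and DGE. In each arm the DGE risks with and without a complication are set so that the arm's overall DGE rate stays at the planned value.

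Worked case, complications 40% (control) v 20% (pyloromyotomy):

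- Control: 0.6 × 0.5415 + 0.4 × 0.8552 = 0.667.
- Pyloromyotomy: 0.8 × 0.3328 + 0.2 × 0.7138 = 0.409.
- Adjusted log odds ratio: logit(0.3328) − logit(0.5415) = −0.695 − 0.166 = −0.86.
- Standardised risk difference, with a mean complication rate of 30%: 0.7 × (−0.2087) + 0.3 × (−0.1414) = −0.189.
- Complication-free subgroup: 0.3328 − 0.5415 = −0.209.

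The same steps for three cases (unadjusted risk difference −25.8 points in each):

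| Complications, control v pyloromyotomy | Adjusted log OR, large sample | Standardised risk difference | Subgroup risk difference |
|---|---|---|---|
| 40% v 20% | −0.86 | −18.9 points | −20.9 points |
| 30% v 30% | −1.19 | −25.8 points | −28.4 points |
| 20% v 30% | −1.33 | −29.1 points | −31.7 points |

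A milder case, 30% v 20% with an odds ratio of 3, gives a standardised difference of about −23.4 points.

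**At the trial's size.** In simulated trials of 64 per arm, with the complication term entering at P<0.15, the mean log odds ratio and power were:

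- 40% v 20%: about −1.08 unadjusted and −0.89 adjusted; power about 82% and 62%.
- 20% v 30%: adjusted −1.36 to −1.39 between runs; power about 83% unadjusted and 93% adjusted.
- 30% v 30%: adjusted about −1.23; power about 84% unadjusted and 88% adjusted.

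The simulated means lie slightly further from zero than the large-sample values, as is usual for logistic regression in small samples. At equal rates the odds ratio still moves, because odds ratios are not collapsible. The standardised risk difference does not move, so there is no bias. Part of the movement at 20% v 30% has the same cause; on the risk-difference scale the inflation there is 29.1 − 25.8 = 3.3 points.

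**Chance selection.** With 10 unrelated, independent candidates (assumed), 10 × 0.15 = 1.5 enter on average, and at least one enters with probability 1 − 0.85¹⁰ = 80%.

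**Subgroup size.** With 20% to 40% complications, 64 × 0.8 = 51 down to 64 × 0.6 = 38 patients per arm remain. Power for the planned effect is then about 75% and 62%.

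**The case against.** The confirmatory analysis is the χ² test, the sample size rests on it, and the plan gives the multivariate model no role in the decision. This stands in full and limits the point to supporting analyses.

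The mechanism that the article proposes is relief of pyloric spasm or dysregulation, not fewer fistulas or abscesses, and it reports no increase in complications in a retrospective analysis. This makes large differences between arms less likely. It does not exclude a decrease, nor a chance imbalance in 128 patients.

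A full protocol or analysis plan, not shown, may list the candidates. The missing list is therefore not the point; the P-value rule is, because the article states it.

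The subgroup's stated purpose is to assess a rate, which is close to descriptive. The definition of primary DGE sets no denominator restricted to complication-free patients, so counting it over all randomised patients already fits the text.

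A reader might infer two stronger things:

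- That adjustment could remove the treatment effect altogether. This would need the whole effect to run through complications, which contradicts the proposed mechanism. No case above removes it.
- That the randomised arm must itself pass P<0.15. At 64 per arm it would then drop out in 6.9% of trials at the planned rates, and in 37.9% at 51.7% v 66.7%. The article applies the screen to risk factors and nowhere says that the arm is screened.

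**Conclusion.** The point holds for the supporting model and the subgroup. The primary test and the sample size are sound on this matter. The stated rule is data-driven and can admit events after randomisation. If complication rates differ between arms, the adjusted effect shifts: by about 7 points towards the null at an assumed 40% v 20%, by about 2 points in the milder case of 30% v 20%, and by about 3 points away from the null at 20% v 30%. With equal rates there is no bias. These sizes rest on assumed complication rates and an assumed strength of association (odds ratio 5, or 3 in the milder case), since the article gives neither. That the subgroup is not a randomised comparison follows from its definition and needs no assumption. The change is worth making because it is nearly free, not because the trial's main conclusion is at risk.

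**What to change.** - For the adjusted treatment effect, use a logistic model with the randomised arm always included and a short list of pre-randomisation covariates fixed before unblinding. Use no P-value selection and no postoperative variables. With 128 × (1 − 0.538) ≈ 59 expected patients without DGE, about five or six covariates is a sensible ceiling.
- Report a standardised risk difference with a 95% confidence interval beside the χ² result. This also avoids the non-collapsibility of the odds ratio.
- Keep any P<0.15 risk-factor model as a separate analysis, labelled exploratory.
- Report the complication-free subgroup descriptively, without a P value, next to complication rates by arm.
- State that primary DGE is counted over all randomised patients, and read it with the complication rates, since more complications in an arm can by themselves lower its count.

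The cost is a change of wording in the analysis plan. Covariates must be chosen in advance, and the subgroup loses any inferential claim. Sample size, conduct and the primary test do not change.

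### Primary DGE and the complication-free subgroup both depend on an event after randomisation: the first can fall because complications rise, and the second is not a randomised comparison

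*Protocol article*

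**What the plan says.** Two analyses in the protocol article are defined by the absence of intra-abdominal complications.

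- Secondary endpoint: the list includes the "rate of primary DGE (defined as DGE in the absence of intraabdominal complications, absolute numbers, percentages". The denominator of the percentage is not stated.
- Data analysis plan: "A subgroup analysis is performed for patients without intra-abdominal complications to assess the rate of DGE in this patient population".

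The context comes from four other places.

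- Randomisation: "Participants will be randomised intraoperatively after absence of macroscopically visible metastases and technical resectability with pylorus preservation has been confirmed". Under Surgical procedures, the allocated manoeuvre precedes the duodenojejunostomy.
- Background: pancreatic fistula, anastomotic leakage, haematoma and abscess "have been associated with the development of DGE in several studies".
- Data analysis plan, general rules: categorical data are compared by χ² or Fisher's exact test, with two-sided P below 0.05 called significant. Neither of the two analyses is exempted or marked as descriptive.
- Data analysis plan, main comparison: "The primary analysis will be conducted in an intention-to-treat" population, on total DGE.

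**The concern.** The complications that define both analyses develop after allocation, and complications are themselves a trial outcome, since morbidity is compared by arm. The two analyses are affected differently.

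- **Primary DGE.** The endpoint is the joint event of DGE and no complication. Raising complications in one arm moves DGE cases out of this category, so the endpoint can improve through harm.
- **Complication-free subgroup.** Restricting to patients who stayed free of complications selects on a post-randomisation event. The patients left in each arm need not be comparable, so a difference in DGE between them is not a randomised treatment effect.

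At stake is how a secondary result is read. A lower primary DGE rate could be reported, with a P-value, as a benefit of pyloromyotomy when it partly or wholly reflects more complications.

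**Working it through.** **The plan's own figure.** The protocol gives no figure for primary DGE or for the subgroup. Its sample size uses "a DGE rate of 40.9% in patients who received intraoperative pyloromyotomy" and "a DGE rate of 66.7% in patients who did not receive pyloromyotomy". With a pooled-variance two-proportion formula, two-sided 5% and 80% power, this gives 58 per arm (power 80.4%), and 58 × 1.10 = 63.8, so 64. The stated 58 and 64 reproduce and are not in question.

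**Order of events.** Randomisation and the manoeuvre take place during the operation. The complications named in the Background follow it. Both definitions therefore condition on something the allocation could influence.

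**Primary DGE as a count or over all randomised.** Let c be the complication rate in an arm, q0 the DGE risk without and q1 the DGE risk with a complication. Assume q0 and q1 are the same in both arms, so the manoeuvre has no effect on DGE at a given complication status.

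- Total DGE = (1 − c)·q0 + c·q1
- Primary DGE over all randomised = (1 − c)·q0
- DGE rate in the complication-free subgroup = q0

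The protocol gives none of these inputs. With assumed q0 = 0.50 and q1 = 0.90:

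| c | Total DGE | Primary DGE, all randomised | Complication-free subgroup |
|---|---|---|---|
| 0.30 | 0.70×0.50 + 0.30×0.90 = 62% | 0.70×0.50 = 35% | 50% |
| 0.40 | 0.60×0.50 + 0.40×0.90 = 66% | 0.60×0.50 = 30% | 50% |
| 0.45 | 0.55×0.50 + 0.45×0.90 = 68% | 0.55×0.50 = 27.5% | 50% |
| 0.50 | 0.50×0.50 + 0.50×0.90 = 70% | 0.50×0.50 = 25% | 50% |

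Against an arm at c = 0.30, the arm with more complications has worse total DGE and better primary DGE.

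The effect does not need complications to cause DGE. Set q0 = q1 = 0.667, so total DGE is 66.7% in both arms. Complications of 30% vs 40% then give primary DGE of 0.70×0.667 = 46.7% vs 0.60×0.667 = 40.0%. At 30% vs 50% it is 46.7% vs 33.4%.

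**Chance of a significant result.** With 64 per arm and a two-sided 5% test (normal approximation):

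- 35% vs 30%: about 9%
- 35% vs 27.5%: about 15%
- 46.7% vs 40.0%: about 11%
- 46.7% vs 33.4%: about 34%

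**Complication-free subgroup.** In the table above the subgroup shows no bias. Bias appears when patients differ in their underlying DGE risk and complications do not strike evenly. Assume half the patients are high risk (DGE 85%) and half low risk (DGE 48.4%), whatever their complication status, so total DGE is (0.85 + 0.484)/2 = 66.7% in both arms. With complication risks h (high-risk half) and l (low-risk half):

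Subgroup rate = [0.5(1 − h)·0.85 + 0.5(1 − l)·0.484] / [1 − 0.5(h + l)]

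- Comparator, h = 0.40, l = 0.20: 0.4486/0.70 = 64.1%
- Extra complications in high-risk patients, h = 0.60, l = 0.20: 0.3636/0.60 = 60.6%
- The same, stronger, h = 0.80, l = 0.20: 0.2786/0.50 = 55.7%
- Complications mainly in low-risk patients, h = 0.20, l = 0.60: 0.4368/0.60 = 72.8%

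The subgroup rate can fall, rise or stay the same, depending on who develops the complications.

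**The case against.** The best case for the plan has five parts.

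- **No reason to expect unequal complications.** The protocol says pyloromyotomy "was not associated with an increased complication rate in a retrospective analysis". This is fair evidence on likelihood, and it is why the rates above are only illustrations. It does not settle the matter: the Discussion names selection bias and incomplete documentation in retrospective studies as a reason for the trial, and the manoeuvres differ physically (electrocautery transection against atraumatic stretching).
- **The denominator may be complication-free patients.** If so, the fall from 35% to 30% disappears under the same inputs. This stands. The directional statement holds only for a count or for a rate over all randomised. With the other denominator, primary DGE becomes the subgroup comparison and shares its weakness.
- **Safeguards exist.** Total DGE is analysed as randomised, morbidity is reported by arm and serious adverse events are compared. This stands in large part: a reader would see total DGE worsen. What the endpoint list does not name is the intra-abdominal complication rate by arm, which is what primary DGE needs beside it.
- **Testing is not explicit for the subgroup.** True. The plan speaks only of assessing the rate there. The general rule makes a test plausible for the secondary endpoint and leaves the subgroup open.
- **Significance by this route would be uncommon.** Also true for moderate imbalances (about 9% to 15%), less so for large ones (about 34%).

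A reader might infer that more complications would also make DGE look lower in the complication-free subgroup. The documents do not support that: the direction depends on which patients are affected, and under the simplest assumptions the subgroup rate does not move. A reader might also infer that pyloromyotomy is expected to raise complications, or that the main result is compromised. Neither follows from the protocol.

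**Conclusion.** The concern holds in a limited form. Both analyses condition on a post-randomisation event that the protocol itself links to DGE, and the article carries no caution.

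For primary DGE as a count or over all randomised patients, the direction is arithmetic: with equal DGE risk among complication-free patients, the arm with more complications scores lower. An assumed 10-point excess in complications gives an apparent 5-point benefit (35% vs 30%) while total DGE worsens by 4 points (62% vs 66%). For the complication-free subgroup, the comparison is not protected by randomisation, and bias may go either way or be nil.

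The sizes rest on assumed complication rates and DGE risks, since the protocol gives no complication rates by arm, and on a denominator that it does not state. The primary comparison of total DGE and the sample size are unaffected. This is a cheap improvement to the reading of one secondary endpoint and one subgroup.

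**What to change.** - State the denominator of primary DGE as all randomised patients in the analysis.
- Report by arm, in one table over these patients, three mutually exclusive categories: no DGE, DGE without an intra-abdominal complication, DGE with an intra-abdominal complication. Place the intra-abdominal complication rate per arm beside it.
- Present primary DGE and the complication-free subgroup as descriptive, without a P-value or causal wording, and note that the subgroup is not a randomised comparison.

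The cost is some analysis-plan wording and one table. The data are already needed to classify primary DGE, and neither the sample size nor the primary analysis changes. The downside is that the sponsor gives up a significance claim for primary DGE.
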